### Statistical Analysis

After summarizing the data, we will use the Kolmogorov-Smirnov test to decide if the data are following a normal distribution. If normally distributed, the student *t* test will be used; otherwise, the z-test will be applied. We will use IBM SPSS (version 26) for statistical analysis. We will set the *P* value to less than .05 for statistical significance.

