### Diagnostic Criteria

The diagnosis of SCH will be made per the *ICD-10* (*International Statistical Classification of Diseases, Tenth Revision*) criteria (SCH) as follows: TSH>4.50 µIU/mL, fT4=0.8-1.8 ng/dL, fT3=1.4-4.4 Pg/mL [13] (Textbox 1).

Eligibility, exclusion, withdrawal, and adverse drug reaction criteria.

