### Screening Investigations

Serum TSH will be measured before and after the study. On the 181st day, serum TSH, T_3_, and T_4_ will be measured. The above findings will be compared to the baseline findings.

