### Criteria of the Assessment or Outcome Variable

A variation of more than 20% of the baseline value of serum TSH with normal values of T_3_ and T_4_ will be considered to determine the efficacy of the intervention. Therefore, decreasing serum TSH with no change in T_3_ and T_4_ means, Kshar Basti with Kanchanar Guggul is efficacious in SCH.

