### Evaluation Outcomes

The primary assessment result of our study is the disparity in the TSH, T3, and T4 levels compared to the initial values. We will deem any deviation of 20% or more from the baseline as statistically significant.

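### The fallback for non-normal data is a z-test, which is the t test with a slightly different cut-off, so the stated rule does nothing for skewed TSH

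*Protocol article*

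**What the plan says.** The Statistical Analysis section is the only place in the article that names a test. It sets a three-step rule:

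- Gate: "we will use the Kolmogorov-Smirnov test to decide if the data are following a normal distribution".
- If the gate is passed: "If normally distributed, the student *t* test will be used".
- If it is not: "otherwise, the z-test will be applied".

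The threshold is a P value "less than .05 for statistical significance"; sidedness is not stated. No transformation, rank test or other skew-tolerant method appears anywhere.

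The rule is applied to the main outcome. Evaluation Outcomes says: "The primary assessment result of our study is the disparity in the TSH, T3, and T4 levels compared to the initial values". Screening Investigations confirms that both values will exist: "Serum TSH will be measured before and after the study". Diagnostic Criteria defines entry as "TSH>4.50 µIU/mL, fT4=0.8-1.8 ng/dL, fT3=1.4-4.4 Pg/mL", which bounds TSH from below and gives no upper limit there. The efficacy criterion is proportional: "A variation of more than 20% of the baseline value of serum TSH with normal values of T_3_ and T_4_ will be considered".

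**The concern.** A fallback for non-normal data should depend less on the shape of the data than the method it replaces. The z-test does not. It is the same comparison of means, referred to a normal instead of a t distribution. If the gate reports non-normality, the rule sends the analyst to practically the same analysis.

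The problem is in what the article states, not in something left for a later document. An analysis plan that followed this rule could not also handle skew; it would have to contradict the rule.

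The main outcome is at stake. A sample selected by a lower TSH cut-off with an open upper end is plausibly right-skewed. A few participants with high TSH would then dominate a raw mean change and inflate its standard error. The raw scale also sits badly with a 20% criterion: 20% is 0.2 × 4.5 = 0.9 units at the entry limit but 0.2 × 10 = 2.0 units at a TSH of 10, so the same relative response counts more than twice as much in a raw mean.

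**Working it through.** **Inputs from the article.** 45 per arm (Grouping; Sample Size Calculations, as 40 + 5); 1:1 allocation (Study Setting); significance level 0.05, taken here as two-sided; entry TSH above 4.50; outcome is change from baseline, taken here as compared between arms. The article gives no figure for the behaviour of the tests that could be reproduced first, and the point does not depend on how N=40 was reached.

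**Step 1: are the two statistics different?** With n per arm, the pooled t statistic has standard error √(2·s_p²/n), where s_p² = (s₁² + s₂²)/2. That equals √((s₁² + s₂²)/n), the standard error of the z statistic. With equal arms the two statistics are identical and only the cut-off differs:

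- t with 2 × 45 − 2 = 88 degrees of freedom: 1.987
- z: 1.960

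Under exact normality, using 1.960 gives a true size of 2·P(t₈₈ > 1.960) = 5.32%.

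**Step 2: what happens to error rates in skewed data?** Simulation of lognormal values, 45 per arm, 20,000 runs per setting, log SD assumed from 0.3 to 1.2. With no true difference the z-test rejected in 4.0% to 5.6% of trials and the t test in 3.7% to 5.3%. Over all settings, with and without a true difference, the two disagreed in at most 1.2% of trials. In the model of step 3, separate runs gave disagreement of 0.5% to 1.7%.

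**Step 3: what does the raw scale cost?** All inputs here are assumptions: population TSH lognormal with median 2.0 and log SD 0.6, within-person log SD 0.2, participants selected at a measured baseline above 4.5, extra response SD 0.3 or 0.5, and 40 per arm (the computed N before 5 are added). Power in %, extra SD 0.3 / 0.5, 1,500 trials per setting:

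| Analysis | True ratio 0.75 | True ratio 0.80 |
|---|---|---|
| z-test on raw change | 81.4 / 53.5 | 60.3 / 35.3 |
| Mann-Whitney on raw change | 82.3 / 55.7 | 60.6 / 36.9 |
| ANCOVA on raw TSH | 81.9 / 52.7 | 59.8 / 33.8 |
| t test on log change | 87.7 / 62.3 | 66.1 / 41.5 |
| ANCOVA on log TSH | 87.1 / 61.6 | 65.2 / 40.9 |

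The Monte Carlo error is up to √(0.5 × 0.5/1500) = 1.3 points per entry. Reading down the columns:

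- Log change minus z on raw change: 6.3, 8.8, 5.8 and 6.2 points. An independent run of z against log-ANCOVA gave 82.6/52.4 against 88.7/60.2 and 60.3/34.3 against 69.3/39.8, which is 6.1, 7.8, 9.0 and 5.5 points.
- Mann-Whitney minus z: 0.9, 2.2, 0.3 and 1.6 points.
- ANCOVA instead of change on the same scale: no gain beyond simulation error, raw or log.

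**Step 4: what if TSH falls in both arms?** Both treatments are meant to lower TSH. With a common fall to 70% of baseline (assumed), z on raw change against log-ANCOVA gave 71 against 87 and 49 against 60 at ratio 0.75, and 52 against 69 and 33 against 41 at ratio 0.80. The gains are 16, 11, 17 and 8 points.

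**The case against.** The strongest reply is that the choice barely matters. The z-test does not require normal data; it requires an approximately normal sampling distribution of the mean, which the central limit theorem largely supplies at about 45 per arm. That stands, and it is why type I error is not the complaint. But the same protection covers the t test, so it gives no reason to switch and does not make the z-test a remedy.

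A reader might infer that the rule inflates the error rate to 5.3%. The documents do not support that. The figure holds under exact normality, the case in which the article uses the t test. In skewed data both tests stay at about 4% to 6%.

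A reader might also infer that power is lost because baseline TSH is not a covariate. That is not supported either. Baseline is used, by subtraction, and covariate adjustment is commonly left to an analysis plan. In the table, adding the covariate gains nothing on either scale. If both arms fall, adjustment on the raw scale would recover part of the gap, but once the analysis is on the log scale it adds nothing.

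Finally, the article gives no TSH distribution, so skew is plausible and not established, and it is uncertain whether the fallback would be reached. In the assumed model a Kolmogorov-Smirnov test with Lilliefors correction rejected normality of change in at least one arm in 61% to 89% of trials; an uncorrected one did so in 4% to 28%. The article does not say which is meant. This also stands, but both branches end in the same raw-scale comparison, so the power cost is much the same either way.

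**Conclusion.** The point holds in a limited form. The stated fallback is wrong as a response to non-normality: it changes a cut-off from 1.987 to 1.960, leaves the statistic untouched and adds no robustness. Nothing elsewhere in the article repairs it.

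The consequence is moderate. Validity under the null is largely intact. What is lost is a summary suited to skewed data and some power: about 6 to 9 points under the assumed model, and up to about 17 if TSH falls in both arms, mainly through the choice of scale. These sizes depend on assumed medians and SDs. With mild skew and no selection (log SD 0.3 to 0.5, unadjusted values) the gap was at most about 4 points. Replacing the z-test by a rank test alone would recover only about 0 to 2 points in the selected-sample model without a common fall.

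The loss still matters, because the Limitations section itself calls 90 a moderate number and expects that dropout may be large.

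**What to change.** Delete the Kolmogorov-Smirnov gate and the z-test. Fix one primary analysis of TSH before any unblinded data are seen: log TSH at day 181 relative to baseline, compared between arms. Either the log change or ANCOVA with log baseline TSH as covariate will serve, since they performed alike; name one. Report the ratio of geometric means with a 95% confidence interval. A 20% relative fall is a ratio of 0.80 on that scale, so the estimate can be read directly against the article's proportional criterion. Add a Mann-Whitney test on change as sensitivity analysis. Because removing the gate also removes the only rule for T3 and T4, name one fixed method for them in the same paragraph.

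The cost is one paragraph of text. Baseline and day-181 values are already collected, and no participants, visits or special software are needed. The small downside is that results appear as ratios and not in mIU/L; geometric means by arm and visit can be shown alongside.

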### Study Setting

This is a single-blind, RCT that aims to determine the superiority of one treatment over another (Figure 1). The study consists of 2 arms and follows a prospective design. Participants will be randomly assigned to either arm in a 1:1 ratio.

The study will be carried out in the Panchakarma department of the hospital affiliated with Mahatma Gandhi Ayurvedic College, hospital, and Research Center (Salod, Wardha district, Maharashtra, India). This study will be conducted following SPIRIT standards for RCTs (Figure 2).

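### The z-test named for non-normal data is the same comparison of means as the t test, so it does not address non-normality

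*Protocol article*

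**What the plan says.** The Statistical Analysis section of the protocol article sets a two-step rule. First, "we will use the Kolmogorov-Smirnov test to decide if the data are following a normal distribution". If the data pass, the Student t test is used; "otherwise, the z-test will be applied". Significance is fixed by setting the P "value to less than .05 for statistical significance", with no sidedness given. The section names no transformation or rank test and does not say whether the t test is paired or unpaired.

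The rule governs the primary result. Under Evaluation Outcomes, "The primary assessment result of our study is the disparity in the TSH, T3, and T4 levels compared to the initial values". Under Screening Investigations, "On the 181st day, serum TSH, T_3_, and T_4_ will be measured". Study Setting describes a two-arm trial that "aims to determine the superiority of one treatment over another", so the comparison of interest is between arms. Efficacy is judged on a relative scale: "A variation of more than 20% of the baseline value of serum TSH", with T3 and T4 normal (Criteria of the Assessment or Outcome Variable).

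**The concern.** The second branch exists to handle data for which the t test is thought unsuitable. A z-test cannot do that. It compares the same two means, needs the same approximately normal sampling distribution, and treats the estimated SD as known, so it assumes slightly more than the t test.

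The branch could well be used. Diagnostic Criteria sets entry at "TSH>4.50 µIU/mL" with no upper limit, so baseline TSH is cut off below and open above, and a relative efficacy criterion suggests proportional effects. Both point towards right skew. In skewed data a few high values drive both the mean and the SD, and a test of raw means uses the information less efficiently than a log-scale analysis or, with more than mild skew, a rank analysis. Power is at stake in a trial whose Limitations section calls 90 participants moderate and foresees possible heavy dropout.

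**Working it through.** **Inputs from the protocol article.** 45 per arm, 1:1 (Grouping; Study Setting); alpha .05, taken as two-sided; outcome on day 181. The calculated 40 per group cannot be reproduced from the text available, which shows no SD, effect or margin value. Nothing below depends on it.

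**Step 1: the two tests compared.** With n = 45 in each arm, both use

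statistic = (mean_A − mean_B) / √[(s_A² + s_B²)/45].

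With equal arms the pooled and unpooled standard errors are the same. Only the cut-off differs:

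- t test, 45 + 45 − 2 = 88 df: 1.987
- z-test: 1.960, lower by (1.987 − 1.960)/1.987 = 1.4%

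For normal data a cut-off of 1.960 on 88 df has size 0.0532. That figure is exact only for normal data, and this branch is reached only when normality has been rejected. The behaviour under skew has to be simulated.

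**Step 2: day-181 TSH.** Assumption: TSH is lognormal, with log-scale SD σ from 0.3 to 1.0. The effect was set to give about 80% power for a t test on log TSH: shift = σ × √(2/45) × (1.960 + 0.842) = 0.591σ. There were 20,000 simulated trials per setting. All entries except σ and skewness are percentages; the last column is in percentage points.

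| σ | Skewness | Type I error, z | Power, z on raw TSH | Power, t on raw TSH | Power, t on log TSH | Power, Mann-Whitney | Loss, z v log |
|---|---|---|---|---|---|---|---|
| 0.3 | 0.95 | 5.2 | 78.6 | 77.7 | 79.4 | 77.4 | 0.8 |
| 0.5 | 1.75 | 5.4 | 74.7 | 73.9 | 79.0 | 77.1 | 4.3 |
| 0.7 | 2.89 | 5.0 | 70.4 | 69.4 | 79.1 | 76.6 | 8.7 |
| 1.0 | 6.18 | 4.6 | 61.3 | 60.0 | 78.9 | 76.9 | 17.6 |

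A repeat simulation put the last loss at about 17 points. Against Mann-Whitney there is no loss at σ = 0.3, then 77.1 − 74.7 = 2.4, 76.6 − 70.4 = 6.2 and 76.9 − 61.3 = 15.6 points.

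**Step 3: arms with different shapes.** With equal means but σ of 0.3 against 0.8, type I error is 7.6% with the z cut-off and 7.3% with the t cut-off. With 0.3 against 1.0 it is 9.8% and 9.5%.

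**Step 4: percent change from baseline.** Assumptions: baseline lognormal with median 6.5 before truncation and log-SD 0.3 or 0.5, kept only above 4.5; within-person log-SD 0.2, 0.4 or 0.6. The z-test on percent change has about 80%, 78% and 74% power, against about 80% for the log ratio of day 181 to baseline. The loss is about 0, 2 and 6 points. In the same settings log day-181 TSH without baseline has only 26% to 73% power.

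**Step 5: the gate.** With samples of 45 and log-SD 0.4, 0.5, 0.6, 0.8 and 1.0, the Kolmogorov-Smirnov test with estimated mean and SD flags lognormal data in 3%, 9%, 19%, 48% and 74% of samples. The Lilliefors-corrected version flags 48%, 68%, 79%, 95% and 99%. The section does not say which is meant, so the branch taken can depend on that choice.

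**The case against.** A reader might infer that the trial has no valid test once normality fails, or that the z-test makes false positives appreciably more likely. The documents and the figures do not support that. With similarly shaped arms the type I error is 4.6% to 5.4%, and slightly conservative under the strongest skew. Where it does rise, because the arms differ in spread and skewness, the t cut-off rises almost as far, so the choice of the z-test is not the cause.

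It is also tempting to say that moving to the z-test loses power. Against the t test it replaces, it gains about 1 point. The shortfall is against methods that the section never names, and a plain t test on raw values would share it. With mild skew, or if percent change is analysed, the loss is small. Under the uncorrected Kolmogorov-Smirnov test, moderately skewed data would seldom reach this branch.

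These objections stand, and they limit the severity. They do not rescue the rule, since a step meant for non-normal data still does nothing about non-normality and no other section corrects it. If the Z statistic of a rank test was intended, the text does not say so and still needs correcting.

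**Conclusion.** The point holds as an error in a stated rule: the z-test is not a remedy for non-normal data. Its consequence is inefficiency rather than invalidity. Relative to a log-scale analysis, the power loss on day-181 TSH runs from about 1 point at log-SD 0.3 to about 17 or 18 points at log-SD 1.0. On percent change it is about 0 to 6 points. Relative to a rank test on day-181 TSH it runs from none to about 16 points. The sizes depend on assumed lognormal TSH, assumed SDs and proportional effects, since the protocol gives no SD and does not say which form of change is tested. The difference in cut-off does not depend on those assumptions. Severity: should be fixed.

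**What to change.** In Statistical Analysis, delete the z-test branch and the Kolmogorov-Smirnov gate. Pre-specify one primary between-arm analysis of TSH that uses baseline: log day-181 TSH adjusted for log baseline TSH, or the log ratio of day 181 to baseline. Report it as a ratio of geometric means with 95% CI, which is on the same relative scale as the 20% criterion. Baseline must stay in the analysis: log day-181 TSH alone would drop the change-from-baseline outcome and, in step 4, much of the power. Name a Wilcoxon-Mann-Whitney test on the change from baseline as the sensitivity analysis.

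The change takes one or two sentences and no new data; baseline and day-181 TSH are already planned. It should be made before the outcome data are examined, so that the primary test is not replaced after a normality result is known. The small downside is that the effect is reported as a ratio rather than a difference in TSH units.

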## Results

### Overview

We will examine the following factors in the demographics: age, gender, location, smoking behavior, alcohol consumption, and the type of salt used to achieve the secondary purpose of this study. We will examine the rate at which participants drop out of the Kshar Basti course, as well as any occurrences of difficulties associated with the Kshar Basti course.

We will only recruit participants for this study once. We will finish the drug preparation and acquisition by June 2024. The projected timeline for the recruitment process is June 2024 to December 2025. We will evaluate the information right away and conclude at the start of 2026.

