**Results:**

Any deviation of the serum TSH by more than 20% from the initial values, while keeping triiodothyronine (T_3_), and thyroxine (T_4_) levels within the normal range, will be deemed statistically significant. Consequently, we anticipate a statistically significant variation in serum TSH levels between the therapeutic enema and Kanchanar Guggul treatments. Presently, the drug preparation operations are in progress. We expect to start enrolling patients in June 2024, do data analysis in December 2025, and acquire results by early 2026, marking the end of this trial.

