##### Course Duration

Basti will be administered daily for 8 days; after that, the participant must follow the regimen for 16 days. The total duration of the course will be 27 days (including Deepan-Pachan for 3 days), and after this course, Kanchanar Guggul will be administered for 153 days. The duration of the therapy will be 180 days, and the follow-up period will be 180 days.

Both groups of patients are restricted from taking or consuming any medications, devices, or nonpharmacological treatments that have an impact on hypothyroidism.

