### Data Collection Methods

The researcher will gather and archive the data. The data will be collected using appropriate software, such as Epi-Info. We will examine the data after the trial concludes. Replicates will be discarded. We will choose a conventional laboratory to quantify serum TSH.

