## Discussion

### Principal Findings

The 45 participants in the control group will receive oral L-thyroxine. On the other hand, the trial group, also consisting of 45 participants, will get a treatment involving Kshar Basti and oral Kanchnar Guggul tablets. Both groups will undergo treatment for 180 days, and on day 181, we will assess the levels of TSH, T3, and T4 in the blood. We will compare the changes before and after therapy. We expect that the Ayurvedic intervention, specifically the combination of Kshar Basti and Kanchnar Guggul, will demonstrate statistically significant outcomes compared to the standard treatment. This would establish Ayurvedic intervention as a viable treatment option for SCH, eliminating the need for lifelong consumption of L-thyroxine tablets by the patient.

Hashimoto thyroiditis typically correlates with hypothyroidism. The thyroid gland produces numerous growth and vasoactive substances. The epithelial cells of the thyroid gland contain the glycoprotein known as vascular endothelial growth factor. It plays a critical role in the elevated levels of TSH in SCH.

A study compared the administration of Nigella sativa powder at a dosage of 2 grams per day for 8 weeks with the administration of placebos consisting of starches at the same dosage and duration. This RCT involved 47 human participants diagnosed with Hashimoto thyroiditis. Nigella sativa treated 23 of them, while starches served as a placebo for the remaining 24. The study determined that Nigella sativa seeds were useful in alleviating Hashimoto thyroiditis. It also successfully reduced vascular endothelial growth factor levels and body weight.

In Ayurveda, Nigella sativa is referred to as “Krishnajeeraka.” In our study, we will be administering Shivakshar Pachak Churna as “Deepan-Pachan” for the first 3 days. Nigella sativa is a constituent of Shivakshar Pachak Churna [16].

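### Recruitment to December 2025, analysis in December 2025 and a day-181 primary outcome cannot all hold

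*Protocol article*

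**What the plan says.** All the relevant statements are in the protocol article.

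- **Recruitment window** (Results, Overview): "The projected timeline for the recruitment process is June 2024 to December 2025".
- **What follows recruitment** (same paragraph): "We will evaluate the information right away and conclude at the start of 2026".
- **Analysis date** (Abstract, Results): "We expect to start enrolling patients in June 2024, do data analysis in December 2025, and acquire results by early 2026". The abstract treats this as the end of the trial.
- **Outcome time** (Screening Investigations): "On the 181st day, serum TSH, T_3_, and T_4_ will be measured". The Discussion, under Principal Findings, repeats it for both arms: "Both groups will undergo treatment for 180 days, and on day 181, we will assess the levels of TSH, T3, and T4 in the blood".
- **When the data are looked at** (Data Collection Methods): "We will examine the data after the trial concludes".
- **Follow-up** (Course Duration): "The duration of the therapy will be 180 days, and the follow-up period will be 180 days". The text does not say whether the two periods coincide or follow one another.
- **Size** (Sample Size Calculations): N=40 per group, raised to 45, for 90 in total.

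**The concern.** A participant needs 180 days between enrolment and the primary measurement. The calendar leaves no such gap between the last enrolment and the analysis, because both fall in December 2025. The forecast for results and conclusion, early 2026, is also too soon for anyone enrolled in the last months of recruitment.

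If the calendar were followed to the letter, one of two things would happen. The trial's only between-arm comparison would be made on the participants who enrolled early enough, fewer than planned. Or outcomes would be compared while others were still on treatment, which the article does not provide for. If the calendar simply slips, the consequence is a later readout than announced. The text does not tell the reader which of these will occur.

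**Working it through.** **Inputs from the article.** Recruitment June 2024 to December 2025; analysis December 2025; results and conclusion early 2026; outcome on day 181, that is enrolment date + 180 days, taking enrolment as day 1; 90 participants, 45 per arm; N=40 per group before the added 5.

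**Assumptions.** The article gives months only, so the start is taken as 1 or 30 June 2024, the end of recruitment as 1 or 31 December 2025, and the analysis as 1 or 31 December 2025. No accrual rate is given. Steps 1 and 2 need none; steps 3 to 5 assume uniform accrual.

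**The article's own duration.** The course adds up: 3 + 8 + 16 + 153 = 180 days. The 180-day interval is therefore not in doubt. The December 2025 analysis date is what cannot be reproduced from the recruitment window.

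**Step 1: last primary outcome.** Last enrolment + 180 days:
- 1 December 2025 + 180 days = 30 May 2026
- 31 December 2025 + 180 days = 29 June 2026

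**Step 2: latest enrolment that yields an outcome at the analysis.** Analysis date − 180 days:
- 1 December 2025 − 180 days = 4 June 2025
- 31 December 2025 − 180 days = 4 July 2025
- 31 January 2026 − 180 days = 4 August 2025
- 31 March 2026 − 180 days = 2 October 2025

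Even with early 2026 read as the end of March, recruitment would have had to stop about two to three months before December 2025.

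**Step 3: share without the outcome, uniform accrual.** Share = (recruitment end − latest usable enrolment) / length of recruitment.

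| Start | Recruitment end | Analysis | Share missing | Of 90 |
|---|---|---|---|---|
| 1 Jun 2024 | 31 Dec 2025 | 31 Dec 2025 | 180/578 = 31% | 28 |
| 1 Jun 2024 | 1 Dec 2025 | 1 Dec 2025 | 180/548 = 33% | 30 |
| 1 Jun 2024 | 1 Dec 2025 | 31 Dec 2025 (lowest) | 150/548 = 27% | 25 |
| 30 Jun 2024 | 31 Dec 2025 | 1 Dec 2025 (highest) | 210/549 = 38% | 34 |

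Across all combinations of start and end, the share is 22% to 27% for an analysis on 31 January 2026, and 11% to 16% (about 10 to 15 of 90) on 31 March 2026.

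**Step 4: number analysed per arm, before dropout.**
- December 2025: (90 − 34)/2 = 28 to (90 − 25)/2 ≈ 33, against N=40.
- 31 March 2026: (90 − 15)/2 ≈ 38 to (90 − 10)/2 = 40, so at or just under N=40.

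**Step 5: sensitivity to accrual.** To have 40 per arm with an outcome by December 2025, 80 of 90 (89%) must be enrolled by 4 June to 4 July 2025. Uniform accrual from 1 June 2024 to 31 December 2025 gives 398/578 = 69% by 4 July 2025. Strong front-loading would remove the shortfall, and late recruitment would deepen it.

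**If the 180-day follow-up comes after therapy.** With 360 days in place of 180, the last participant finishes between 26 November and 26 December 2026. No measurement is scheduled after day 181, so this affects the trial's end date and not the primary outcome.

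**The case against.** The strongest reply is that the dates are forecasts, not analysis rules. The article calls the recruitment timeline projected and the analysis date expected, and its Statistical Analysis section sets no calendar cut-off. Data Collection Methods says the data are examined after the trial concludes. On that basis the natural result of a slipping calendar is a later readout. This largely stands. A reader might infer that the article plans a subset analysis or an unannounced interim look, but nothing in it authorises either. It does not dispose of the point, because the conclusion of the trial is not defined as the last day-181 visit, and the abstract itself has the trial ending with results in early 2026.

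A reader might also infer that about a third of participants will lack the outcome and that the analysis will fall below 40 per arm. The documents do not support either as a flat statement. Both need uniform accrual, which is not stated, and enforcement of a forecast date. By 31 March 2026 the shortfall is about two per arm at most under uniform accrual.

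A third tempting inference is that the trial cannot end before late 2026. That requires the 180-day follow-up to come after therapy, which Course Duration leaves open, and that period has no stated endpoint.

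Finally, the recruitment process might be meant loosely as the whole period of trial conduct, which would remove the conflict. The text does not say so, and the same paragraph uses recruiting in its ordinary sense. If that was the meaning, the real recruitment close is missing and the sentence still needs correcting. That the article condenses a fuller protocol does not help either: the problem is stated dates that disagree, not an omission.

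**Conclusion.** The point holds as a contradiction between stated dates. Independently of accrual, participants enrolled after about 4 June to 4 July 2025 have no primary outcome at a December 2025 analysis, and the primary data cannot be complete before about 30 May to 29 June 2026.

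The size of the loss is conditional. Under uniform accrual it is 27% to 38% of participants in December 2025, leaving about 28 to 33 per arm against N=40 if that date were enforced, and 11% to 16% at 31 March 2026. A delayed readout is at least as plausible a consequence as a truncated analysis, so the finding is that the plan must be made consistent. It is not that a biased or early analysis is intended.

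**What to change.** Choose one of two routes and use the same wording in the abstract's Results, in Data Collection Methods and in the Results Overview.

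1. **Keep the recruitment window.** State that there is a single data lock and analysis after the last randomised participant's day-181 visit, about the end of June 2026 on the current window, and that no outcome comparison between arms is made before it. Cost: a text change and about six months' later readout.
2. **Keep the December 2025 analysis.** Close recruitment by about 4 June to 4 July 2025, according to the day in December on which the analysis starts. Cost: a text change and a shorter window. From a 1 June 2024 start it falls from up to 578 days to 368 to 398 days, so reaching 90 would need accrual about 1.45 (578/398) to 1.57 (578/368) times as fast.

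Under either route, reconcile Course Duration by stating whether the 180-day follow-up runs alongside therapy or after it, and define the end of the trial accordingly. If the follow-up comes after therapy, say what is measured in it and whether the primary analysis waits for it.
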